### Objectives

The primary aim of this study is to evaluate the feasibility and acceptability of an intervention that combines an economic intervention with a self-regulation intervention among adolescents living in urban poverty in Bogotá (Colombia), Kathmandu (Nepal) and Cape Town (South Africa). This will be done by assessing the following criteria (which have been defined as progression to full trial criteria): (1) fidelity across intervention arms; (2) participants attending sufficient intervention sessions; (3) reported adverse events across intervention arms compared to control arm; (4) reported negative experiences related to cash transfers, as well as qualitative perspectives on acceptability of interventions; (5) baseline differences in demographic variables across arms for adequacy of randomisation; (6) adequacy of masking; (7) missing values on outcome instruments; (8) loss to follow-up across timepoints. Furthermore, we aim to evaluate the sensitivity to change on study participants’ clinical and non-clinical outcomes. The study is part of the ‘Improving Adolescent mentaL health by reducing the Impact of poVErty (ALIVE)’ project, which has been introduced elsewhere [12].

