### Instruments

Four types of data are being collected: (1) intervention implementation outcomes (to assess feasibility); (2) adolescents’ outcomes (to assess sensitivity to change), including self-report instruments, physiological measures and neuropsychological tasks; (3) caregiver outcomes (all self-reported instruments, to assess sensitivity to change); and (4) costs (to assess feasibility). All self-reported instruments and neuropsychological tasks included in the assessment have been adapted in each site as part of the ALIVE project. These are described in more detail below and reported in Tables 5 and 6. Unless otherwise stated, all adolescent and caregiver outcomes are assessed at all timepoints. Full adolescent and caregiver assessments are also available in supplementary files 3 and 4.

**Table 5 Tab5:** Overview of self-report adolescent instruments

Name	Domain	Construct	# Items	Responses/Scoring	Country/Regional Psychometrics	Time (minutes)
Demographics	Demographics	Age, gender, ethnicity, etc	17	Multiple response options; used as individual item covariates in analyses	Not applicable	2
Education (Risk score items: [36]) - Schooling	Education	Educational status, disruptions	16	Multiple options; used as individual item covariates in analyses; items contribute to calculation of IDEA Risk Score	Not applicable for individual items; IDEA-RS c-statistic described below	2
Measurement of Mental Health among Adolescents and Young People at the Population Level (MMAPP) [37]	Mental health	Anxiety, depression	28	Frequency of symptoms (4 options, 0 never to 3 always); Total PHQ-A and GAD-7 score; depression caseness (score > = 16 (South Africa), > = 15 (Nepal), > = 14 (Colombia)); anxiety caseness (score > = 12 (Colombia and South Africa), > = 10 (Nepal))^A^	Depression: Colombia (≥ 14): 0.72 (sens); 0.74 (spec) Nepal (≥ 15): 0.88 (sens); 0.83 (spec) SA (≥ 16): 0.75 (sens); 0.79 (spec) Anxiety: Colombia (≥ 12): 0.71 (sens); 0.76 (spec) Nepal (≥ 10): 0.58 (sens); 0.64 (spec) SA (≥ 12): 0.69 (sens); 0.73 (spec)	6
Disruptive Behaviour International Scale (DBIS) [38]	Mental Health	Oppositional defiant disorder, conduct disorder	8	Frequency of symptoms (4 options, 0 never to 3 always); Total disruptive behaviour symptom score (sum of all items)	Nepal only: Cronbach’s *α*: 0.84; test–retest reliability (intraclass correlation 0.93, *r* =.93) [38].	1

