
The adolescent assessment will also include heart rate variability (HRV), which is the variation between beat-to-beat intervals. HRV has consistently been shown in meta-analyses to correlate with stress [59], anxiety [60], depression [61] and self-regulation [62]. We will measure 5-min resting state HRV using either a wearable ECG device, the Polar H10 chest strap, which is a well-validated method for measuring HRV [46, 47], or when not feasible, a photoplethysmography (PPG) Bluetooth earlobe device from HeartMath (www.heartmath.com), which has also demonstrated acceptable accuracy at rest [63]. Data will be recorded using the HRV logger application, using a similar procedure as reported by [64]. Since body mass index can explain some of the variance in HRV, weight and height will also be recorded and controlled for [65]. HRV assessments were “resting state” measures, so physical activity was standardised. However, the HRV measures were taken at different times of day, depending on scheduling in schools, so this was not standardised [66].

Finally, three neuropsychological tasks, which have been culturally adapted for the three ALIVE contexts, will also be administered: the Balloon Analogue Risk Task – Youth version (BART-Y) [67], the Emotional Go No-Go Task [68] (in Colombia and South Africa) and the Delay Discounting Task [69]. The BART–Y assesses decision-making and is a computerised measure of risk-taking behaviour balancing the potential for reward versus loss. The original BART includes cash as a reward, which are converted to prizes in the BART-Y. However, several studies have demonstrated that tasks using hypothetical rewards provide valid measures of risk taking [70]. The task will therefore use a points accumulation displayed in the BART-Y, rather than cash or prizes.

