**Feasibility of the study procedures**				
Feasibility of randomisation	Difference in participant recruitment rate between arms	1. > 60% participants agree to be (i) re-screened to determine eligibility for the pilot, or (ii) enrolled into the pilot (when second screening for pilot does not take place) 2. > 30% difference in recruitment rate between arms	1. > 60% participants agree to be (i) re-screened to determine eligibility for the pilot, or (ii) enrolled into the pilot (when second screening for pilot does not take place) 2. 20–30% difference in recruitment rate between arms	1. > 60% participants agree to be (i) re-screened to determine eligibility for the pilot, or (ii) enrolled into the pilot (when second screening for pilot does not take place) 2. < 20% difference in recruitment rate between arms
Feasibility of masking research assistants	Self-report questions at the end of each assessment	> 50% guess correct arm	35–50% guess correct arm	< 35% guess correct arm
Feasibility of data collection	Proportion of missing items on the GAD-7 and PHQ-A items at 18 month follow-up	> 20% missing	10–20% missing	< 10% missing
Feasibility of retention	Proportion of recruited adolescents lost to follow-up (LTFU) at 18-month follow-up	> 30% LTFU	20–30% LTFU	< 20% LTFU

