## Discussion

The aim of the study is to test study procedures and assess the feasibility and acceptability of a new intervention combining self-regulation and economic components to prevent depression and anxiety among adolescents living in urban poverty. Given the bidirectional relationship between poverty and poor mental health, there is a need to generate evidence on the effectiveness of interventions which address both aspects simultaneously. With this study, we expect to meet criteria for progression to full trial that have been established for intervention implementation (i.e. fidelity, retention, adverse events, experience with cash transfers) and trial procedures (i.e. randomisation, masking, data collection, retention, contamination), as well as demonstrating sensitivity to change on all self-report and neuropsychological outcome measures, primarily among participants in the combined intervention arm. From this pilot trial, we will learn whether the interventions, and especially the cash transfer, had any negative impact (e.g. perceived inequity, reduced motivation), and how these can be better mitigated in a future trial. Equally we want to understand whether and how contextual factors might influence aspects of feasibility—especially given the three different study sites (e.g. levels of poverty, gender or cultural factors, across and within the Colombia, Nepal and South African samples). For any of the above findings, we will review if and what changes can be made to address any biases or improve procedures or intervention content.

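### The data-collection progression criterion checks PHQ-A and GAD-7 items at 18 months only, although the future primary outcome draws on every follow-up visit

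*Protocol article*

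**What the plan says.** The Objectives section lists eight criteria, "which have been defined as progression to full trial criteria". One of them is "7) missing values on outcome instruments", with no restriction to particular scales or to one visit. The Instruments section describes adolescent outcomes as "including self-report instruments, physiological measures and neuropsychological tasks".

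Table 7 turns this objective into one row, Feasibility of data collection. Its indicator is "Proportion of missing items on the GAD-7 and PHQ-A items at 18 month follow-up". Below 10% is green, 10–20% amber and above 20% red. No other row of Table 7 counts missing outcome data; loss to follow-up at 18 months has its own retention row.

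The section on adolescent outcome instruments names PHQ-A and GAD-7 as the primary outcomes of the future trial. It defines that outcome as cumulative incidence: above the depression and/or anxiety cut-off at one or more follow-ups. The section on sensitivity to change repeats this. It explains that a count at 18 months alone was rejected because it would miss adolescents who became cases earlier and had recovered by then.

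**The concern.** The row is meant to tell the sponsor whether the data for the definitive trial can be collected. It looks at one of the three visits from which the primary outcome is built. The protocol argues that the earlier visits hold cases which 18 months would miss, yet its data-collection check ignores those visits.

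A green rating means that progression can go ahead with no adaptation. If many PHQ-A or GAD-7 items were missing at T1 or T2, the rating would give that assurance wrongly, and the event rates passed on to the sample size calculation would rest on incomplete caseness data.

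A second, smaller gap concerns the other measures. Heart rate variability is recorded with a chest strap, "or when not feasible, a photoplethysmography (PPG) Bluetooth earlobe device", and "three neuropsychological tasks, which have been culturally adapted for the three ALIVE contexts, will also be administered". The Discussion looks forward to "demonstrating sensitivity to change on all self-report and neuropsychological outcome measures". Table 7 has no place where completeness of any of these is recorded, although Objective 7 reads as if it covers them.

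**Working it through.** **Inputs.** Bands: green <10%, amber 10–20%, red >20% (Table 7). Visits: T0 baseline, T1 post-intervention, T2 12 months, T3 18 months (Procedures). Enrolled adolescents: 160 + 229 + 239 = 628 (Table 4, reproduced). The documents give no missingness rate for any instrument, so the percentages below are assumptions shown over a range.

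**Step 1: what the row responds to.** Let m1, m2 and m3 be the shares of PHQ-A/GAD-7 items missing at T1, T2 and T3. The row's colour depends on m3 alone. Take m3 = 5% and m2 no larger, and vary m1:

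| m1 | Row as published (m3 = 5%) | Worst follow-up visit, max(m1, m2, m3) |
|---|---|---|
| 0% | green | 5%, green |
| 10% | green | 10%, amber |
| 20% | green | 20%, amber |
| 25% | green | 25%, red |
| 50% | green | 50%, red |
| 100% | green | 100%, red |

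The same holds with m1 and m2 exchanged. The insensitivity follows from the definition and does not depend on the chosen values.

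**Step 2: what this does to the outcome.** Cumulative incidence is the share above a cut-off at T1 or T2 or T3. Let q1 be the share of adolescents above a cut-off at T1 only, and u1 the share without a usable T1 score. If u1 is unrelated to caseness and an unknown status is counted as no case, the estimate falls by u1 × q1. With u1 = 25%, a quarter of the T1-only cases is lost. The documents give no value for q1, so the absolute fall cannot be stated.

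In numbers of adolescents: if all 628 were assessed at T1 and the missing items fell entirely on 25% of them, 0.25 × 628 = 157 would have no T1 caseness status, and the row could still be green.

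**Step 3: the other measures.** Heart rate variability and task data enter neither numerator nor denominator of the row. Any loss from 0% to 100% leaves its colour unchanged.

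**The case against.** The strongest defence is that Table 7 decides progression to a trial whose primary outcomes are PHQ-A and GAD-7, so gating on those two scales is coherent. Objective 7 does not say all instruments, and the table may be read as its operational definition. Heart rate variability and the tasks are secondary. They can be described outside the traffic lights, the qualitative interviews cover barriers to completing assessments, and a detailed analysis plan is promised. All of this stands as regards the choice of scales. It does not answer the choice of visit: an argument from the primary outcome requires T1 and T2 as well as T3.

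Multiple imputation among those followed up may recover some information. It does not make the row register the loss.

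A reader might infer more than the documents support:

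- **That lost heart rate variability or task data should block progression.** Nothing in the protocol requires this. No loss rate is given for these measures, so a figure such as 50% invalid recordings is purely hypothetical. The earlobe device is also a safeguard against loss.
- **That Nepal shows a data-collection failure, with 0 of 229 adolescents having Emotional Go No-Go data.** The task was not used there because the local stimuli were poorly recognised. Data never planned are not missing values.
- **That one event is scored twice, with 25% loss to follow-up amber for retention and red for data collection.** This requires counting lost adolescents as missing items. The separate retention row and the planned imputation among those followed up make that the less natural reading.
- **That PHQ-A and GAD-7 items are the data least likely to be missing.** The documents do not show this. In South Africa the questionnaires are self-administered in small groups, so item non-response is a real question there.

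**Conclusion.** The point holds as a mismatch of scope. The criterion covers one of the three follow-up visits that define the future primary outcome, and is narrower than Objective 7 as worded. Its size is structural: at 5% missing at 18 months, no amount of item loss at T1 or T2 moves the row from green. Whether such loss occurs is unknown from the documents, and the effect on cumulative incidence depends on how many adolescents are cases at an earlier visit only.

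The gap for heart rate variability and the tasks is one of reporting. It does not show that the progression decision rests on the wrong scales. The matter should be corrected because it changes what a green rating can support; it does not undermine the pilot's design.

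**What to change.** In Table 7, score PHQ-A/GAD-7 item missingness among adolescents assessed at each of T1, T2 and T3, keep the existing bands, and let the worst follow-up visit set the colour. Report T0 as well. State that loss to follow-up is scored in the retention row only, and print the number assessed at each visit so that a missed T1 or T2 visit is visible.

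Separately, tabulate by visit and country the share of valid heart rate variability recordings and of completed runs of each task, only where the measure was planned (so not Emotional Go No-Go in Nepal). Use the table to decide whether each secondary measure is kept, changed or dropped, without gating progression. If the sponsor does not want this, narrow the wording of Objective 7 to match Table 7.

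Because enrolment is complete, make the change a dated addition, say whether missingness counts were already known, and report the published 18-month row beside it. The cost is a few lines of text and simple counts from data already being collected. The downside is that the row, or some secondary measures, may be rated less favourably.

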### Control condition

The control group follows a “care as usual” approach, which means it is a no active comparator condition. This is in line with a decision framework for the selection of control condition in randomised controlled trials [29], considering the ALIVE interventions can be categorised as an early phase trial and as low-risk. We also want to compare our intervention arms with the reality of what adolescents currently receive in these communities. Finally, there is genuine equipoise about the effects of self-regulation and economic interventions (including cash transfers) on the prevention of depression and anxiety. This also justifies not giving cash to the self-regulation and control arms at the end of the intervention.

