### Sample size

We aimed to recruit a sample of 240 adolescents (13 − 15 years), living in poor urban households in each country, with an equal sample size in each of the four trial arms (*n* = 60). This study is not powered to evaluate effectiveness [32] but instead aims to test trial procedures, based on which parameters can be defined to run sample size calculations for the adequately powered RCT. We followed recommendations for sample size requirements to estimate key design parameters for pilot trials, which suggest at least 240 measured participants (60 per group) when estimating the Experimental Event Rate [33]. Thus, we aimed to recruit 30 adolescents and their caregivers per school, for a total of 60 adolescents and their primary caregiver per arm.

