### Data analysis

#### Analyses of criteria for progression to full trial

The primary analyses for this pilot cRCT concern the assessment of a priori defined criteria that will be used for decision making for progression from pilot trial to an adequately powered trial. These criteria will be scored using a “red” (study cannot progress “as-is” but will require major adaptations to content or procedure), “amber” (progression can happen, but small adaptations should be considered to improve content of procedure) and “green” scoring (progression can happen without any adaptations). The criteria are listed in Table 7 and pertain to the feasibility of randomisation, data collection, masking and retention, as well as fidelity and adherence to ALIVE interventions, (severe) adverse events and safety of the cash transfers.

**Table 7 Tab7:** Criteria for progression to full trial

Criteria item	Indicator/measure	Alternative traffic light system		
		Red	Amber	Green

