**Feasibility of intervention**				
Fidelity to ALIVE interventions	Average fidelity across intervention arms, based on Fidelity checklists completed for 10 − 15% of the sessions by trainer/supervisors	< 60% Fidelity	60–75% Fidelity	> 75% Fidelity
Adherence to intervention	Attendance data at each session, as reported on TeamPact	Retention of < 50% of participants through adequate completion of sessions (i.e. > 70%), in each intervention arm	50–70% retention in each intervention arm	> 70% retention in each intervention arm
Presence of (severe) adverse events	Across all active arms compared to control arm	> 20% increase	10–20% increase	< 10% increase
Safety of the cash transfer	Post session feedback from facilitators; Interviews with adolescents and caregivers; (S)AEs	> 30% participants report a negative event	10–30% participants report a negative event	< 10% participants report a negative event

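### The Table 7 retention criterion has no arm input, so it can score green while loss to follow-up differs widely between arms

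*Protocol article*

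**What the plan says.** The retention row of Table 7 (Feasibility of the study procedures) has one indicator: "Proportion of recruited adolescents lost to follow-up (LTFU) at 18-month follow-up". Its limits are green below 20%, amber 20–30% and red above 30%. The Objectives list the matching criterion as "8) loss to follow-up across timepoints", that is, by visit and not by arm.

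Other rows of the same table do bring in arm. The randomisation row uses "Difference in participant recruitment rate between arms", with limits at 20% and 30%. The adherence row is set for each active arm (amber is "50–70% retention in each intervention arm"). The adverse-event row is assessed "Across all active arms compared to control arm".

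The section on progression criteria defines green "scoring (progression can happen without any adaptations". It presents the criteria as fixed in advance and as the pilot's primary analysis.

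The economic and combined arms receive six cash transfers over 4–6 months. The self-regulation and control arms receive none, and the Control condition section rules out cash for them at the end as well: "This also justifies not giving cash to the self-regulation and control arms at the end of the intervention".

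**The concern.** The row reduces four arms to one proportion. A pilot in which two arms keep nearly everyone and two lose a third can get the same colour as one with equal, moderate loss in every arm. Only the first threatens the comparison of arms.

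That comparison is what the pilot prepares for. The sensitivity-to-change section gives the full trial's primary contrast as the proportion in each arm who exceed a depression or anxiety cut-off at any follow-up. If loss differs between arms and those lost differ in risk from those retained, this contrast is biased even with no true effect.

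Unequal loss is plausible here because the arms differ in what participants receive: cash and sessions in two arms, sessions alone in one, neither in the control. The consent section shows that the authors had arm-linked attrition in mind, since it withholds the content of other arms partly to protect against it. An analysis plan may well tabulate loss by arm, but that would not change the colour this rule gives.

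**Working it through.** **Inputs from the protocol article.** 30 adolescents per school, two schools per arm, four arms, so 30 × 2 × 4 = 240 per country, which is the stated target ("with an equal sample size in each of the four trial arms", n = 60). Enrolled: 160 + 229 + 239 = 628, matching Table 4. Retention limits: 20% and 30%.

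**1. Gaps that still score green.** With equal arms, overall loss is the mean of the four arm rates.

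- 5%, 5%, 33%, 33%: (5 + 5 + 33 + 33)/4 = 19%. Green, with a 28-point gap and two arms above the table's own red limit.
- In whole persons at 240: the most losses that stay below 20% is 47 (47/240 = 19.6%). Splitting them 6/120 in cash arms and 41/120 in no-cash arms gives 5.0% and 34.2%, a gap of 29.2 points. The extreme, 0/120 and 47/120, gives 39.2 points.
- On the enrolled numbers, assuming equal halves because enrolment by arm is not given, the largest gap still green is 38.8 points (Colombia), 39.3 (Nepal), 39.3 (South Africa) and 39.8 (all 628).
- One arm can also hide: 10% in three arms and 49% in control gives (3 × 10 + 49)/4 = 19.75%, green.

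**2. What such a gap could do to the outcome.** Assume true incidence p in every arm, loss L, and risk ratio RR in those lost relative to those retained. If those lost contribute no outcome, observed incidence = p / (1 − L + L × RR). The documents give neither p nor RR; both are assumptions. Loss is 5% (cash) and 33% (no cash).

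| p | RR | Cash | No cash | Spurious difference |
|---|---|---|---|---|
| 20% | 1.5 | 19.5% | 17.2% | 2.3 points |
| 20% | 2.0 | 19.0% | 15.0% | 4.0 points |
| 30% | 1.5 | 29.3% | 25.7% | 3.5 points |
| 30% | 2.0 | 28.6% | 22.6% | 6.0 points |

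In every row cash looks harmful when it has no effect. With an RR below 1 the sign reverses. With equal loss in all arms the difference is zero.

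**3. If T1 and T2 are kept for those missing T3.** Assume an independent 10% chance of a positive screen per visit. Three visits give 1 − 0.9³ = 27.1%; two give 1 − 0.9² = 19.0%. Cash: 0.95 × 27.1 + 0.05 × 19.0 = 26.7%. No cash: 0.67 × 27.1 + 0.33 × 19.0 = 24.4%. The difference is 2.3 points even though loss is unrelated to risk, because fewer visits mean fewer chances to be counted.

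**4. Two possible remedies, checked for false alarms.** Assume a true loss of 15% in every arm.

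- Worst single arm on the 20% limit: the chance that at least one of four arms reaches 20% is 1 − P(one arm below 20%)⁴, which is about 55% at 60 per arm and 67% at 40 per arm (160/4). The overall rule misfires about 2% and 5% of the time. Clustering is ignored.
- Cash versus no-cash difference of 20 points: reached by chance in under 2% of simulated trials per country, even with an assumed intracluster correlation of 0.05.

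**The case against.** A reader might infer that cash-driven loss is the pattern most likely to bias this design. The documents do not support that. They give no expected loss by arm, and several features work against a large gap at 18 months: cash stops after 4–6 months, about a year before the last visit; assessment vouchers are set by country and not by arm; and participants are not told what other arms receive until after the 18-month assessment. The 5%/33% split is an illustration, not a forecast.

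A reader might also infer that a green score means the pilot will declare retention free of problems. That too goes beyond the text. The Discussion lists retention among the procedures to be examined and undertakes to consider changes that address biases. The colour is not the only route to adaptation.

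The bias formula in step 2 drops everyone lost at 18 months, yet someone positive at T1 or T2 is already a case. This is correct, and it is why the size is given as a rough range with a separate figure for retained visits. The pilot itself makes no formal test between groups, so the harm would fall on the full trial. An overall loss limit is also a legitimate simple threshold.

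These points limit the size and certainty of the problem. They do not answer the structural one: while total loss stays below 20%, the rule cannot register a difference between arms, although neighbouring rows do bring in arm.

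**Conclusion.** The point holds as a gap in a pre-set decision rule. The retention row has no arm input and can be green with a cash versus no-cash gap of up to about 39 points. This rests on reading the row as one proportion over all recruited adolescents. The table does not use the word overall, nor does it say whether scoring is per country or pooled, but other rows name arms when arms are meant.

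How large a gap will occur is unknown from the documents. Under the assumptions stated, a 5%/33% split would give a spurious difference of roughly 2 to 6 percentage points if those lost contribute no outcome, and a different amount if T1 and T2 data are kept. The direction depends on whether those lost have higher or lower risk. The change is worth making because it is cheap and concerns the full trial's primary contrast; it does not undermine the pilot's other criteria.

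**What to change.** Keep the overall 20%/30% bands and add a second condition to the retention row: the difference in 18-month loss, in percentage points, between cash and no-cash arms and between active and control arms. The 20%/30% difference limits of the recruitment row could serve. The row takes the worse of the two colours. Score the difference pooled over countries, and report loss by arm and country with intervals.

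Both contrasts are needed. The 5%/33% example gives 28 points for cash versus no cash (amber), but only 33 − (5 + 5 + 33)/3 = 18.7 points for control versus active. The example with 49% in control gives 39 points for control versus active (red), but only (10 + 49)/2 − 10 = 19.5 points for no cash versus cash.

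Do not score by the worst single arm. At 40–60 per arm it would turn amber by chance more often than not under a uniform 15% loss, and it would make a 20%/30% difference condition redundant.

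The cost is table wording and a cross-tabulation of data already collected. Green becomes slightly harder to reach. With two schools per arm per country the figures are imprecise: at 120 versus 120 the 95% half-width is about 9–10 points before clustering, so country-level gaps should be read descriptively. If loss by arm has already been seen when the condition is added, say so and label it as added afterwards.
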